## Abstract

**Background:**

Cervical cancer is one of the most common cancers in women and could be prevented by human papilloma virus (HPV) vaccination. *Cervarix*, the first available HPV vaccine, has been widely administrated to Chinese women, while little was known about its effect on the prevention and control for HPV related diseases in China. The study aims to assess the impact of *Cervarix* on HPV infection and cervical related diseases in real world.

**Methods:**

This is a prospective, multi-age birth cohort study to investigate the incidence and continuous status of HPV infection, and relevant cervical diseases by exposure status (with *Cervarix* vaccination history or without any HPV vaccination history). It is planned to recruit 12,118 eligible women at age of 9 to 45 years from vaccination clinics or hospital outpatient clinics, and then follow up them for three years. The standard questionnaire will be used to collect information such as demographic characteristics, menstruation and obstetrical histories, history of sexual behavior, personal behavior history, history of disease and pathogen infection, medication history, and family history at baseline. After three years, the changes of these behaviors will be investigated again, and other related health status information will be retrieved from the electronic health records during the follow-up period. If available physically and legally, the cervical cancer screening will be performed, including type-specific HPV deoxyribonucleic acid (DNA) polymerase chain reaction (PCR) testing and contingent thinprep cytologic test (TCT) and colposcopy. The free cervical cancer screening will be captured and uploaded timely to the Yinzhou Regional Health Information Platform (YRHIP); therefore, the long-term outcomes of participants will be monitored.

**Discussion:**

This prospective cohort study will assess the impact of HPV vaccine on HPV infection and related cervical diseases in women aged 9–45 years, which makes up for the lack of evidence in Chinese women. The results of this study will provide support for understanding the impact of HPV vaccination in China, and make a contribution to increasing HPV vaccination and cervical cancer screening coverage in China.

**Trial registration:**

This study has been retrospectively registered on *clinicaltrials.gov* (NCT05341284) on April 22, 2022.

## Background

Cervical cancer was the fourth most common cancer in women, with approximately 0.60 million cases and over 0.34 million deaths from cervical cancer worldwide in 2020 [1]. China is one of the countries with the most cases contributed with approximately 0.11 million cases and 0.05 million deaths [2]. Further, both the incidence of cervical cancer and disease burden still increased in the last decades, and its onset age becomes much younger in Chinese women [3, 4]. Human Papillomavirus (HPV) infection is the primary cause of cervical cancer [5], specifically, HPV16 and 18 infections accounted for 84.5% of invasive cervical cancer in China [6].

Expanding the coverage of HPV vaccines is an essential part of the 90–70-90 target proposed by the World Health Organization (WHO) for eliminating cervical cancer [7]. In a modeling study, with 70% coverage of bivalent vaccine, cancer cases can decrease by 58% to 33% in rural areas and 69% to 32% in urban areas at ages of 12 to 55, respectively [8]. China has also been making effort to increase vaccination coverage. Since 2016, HPV vaccines have been introduced for females aged 9–45 in mainland China, such as *Cervarix* (9–45 years old) in 2016, *Gardasil 4* (20–45 years old) in 2017, *Gardasil 9* (16–26 years old) in 2018 and the domestic bivalent HPV vaccine *Cecolin* (9–45 years old) in 2019 [9–12]. These vaccines were not included in the programmed immunization and were paid for by the receivers. Since 2020, some of cities in China have launched free HPV vaccination programs for girls under 14 years, which only included the domestic bivalent HPV vaccine *Cecolin* for now [13, 14]. In addition, China is also popularizing cervical cancer screening to accelerate the elimination of cervical cancer. China has initiated *the Two Cancers (the cervical cancer and breast cancer)* Screening Program in 2009, which provided females aged 35 years and over with cervical cancer and breast cancer screening for free [15]. Screening strategies varied across regions, including HPV-initiated and TCT-initiated tests. As for Yinzhou, Ningbo, where our study will be conducted, the standard cervical cancer screening process initiate with a type-specific HPV DNA PCR testing, and for the ones with HPV infection will be referred to colposcopy or cytology test, while those who are tested negative will be invited for another screening after 3 years (Fig. 1).

**Fig. 1 Fig1:**
[figure not shown]
Cervical cancer screening procedure

Several prospective cohort studies assessed the impact of HPV vaccination, such as a Dutch prospective cohort initiated in 2009 [16], a 10-year prospective cohort study in Greece between 2009–2019 [17], a population-based birth cohort study in Sweden [18], and a register-based cohort study in Denmark [19]. These cohorts consistently provided supportive evidence for the effectiveness of HPV vaccination and its policies. However, there are no such studies conducted in China, where the promotion of HPV vaccines seems much more pressing. *Cervarix,* the first available HPV vaccine for Chinese women, have great acceptance in China [20]. Here, as an exemplar, the prospective cohort study with *Cervarix* assesses the impact of HPV vaccination on HPV infection and cervical related diseases in Chinese women. The indicated population of Cervarix are females aged 9–45, thus, the whole indicated population should be included into the real-world study. In addition, the age distribution of HPV-infected population in China is bimodal (< 25 years and 41–45 years) [21], therefore, it is also important to evaluate the role of HPV vaccination in women aged 41–45 years in China.

Yinzhou, in which this study will be conducted, is a district of Ningbo, Zhejiang province, which is one of the most developed provinces of China. The Center for Disease Control and Prevention (CDC) of Yinzhou set up an integrated electronic health information system for local residents in 2005 [22]. By the year of 2009, this regional system has covered nearly all health-related activities of residents from birth to death. For its high population coverage and superior data quality, this platform is identified as one of the best sources of post-marketing drug surveillance in China. Hence, we choose to conduct our study in this area and use this platform to manage our data, which will allow us to expand the follow-up period in a real-world setting.

### Aims

The study aims to evaluate the impact of the AS04 adjuvanted HPV 16/18 vaccine (Brand name: *Cervarix),* for HPV infection and related cervical diseases in real world, with the following objectives:To describe the incidence of HPV 16/18 infection by exposure status, and to evaluate the effectiveness of *Cervarix* on HPV 16/18 infection in birth cohortsTo describe the incidence of cervical lesions or diseases, and other 12 high-risk HPV infection by exposure status in birth cohorts

## Methods

### Study design and setting

Prospective, multi-age birth cohort study to investigate the incidence and its change of HPV infection and relevant cervical disease by exposure status (with *Cervarix* vaccination history or without any HPV vaccination history) in recruited subjects between 9 to 45 years old in Yinzhou District. Participants of this study will be recruited from local vaccination sites and the hospital outpatient clinics, and they will be divided into three age groups (9–20 years, 21–30 years,31–45 years) at baseline. Participants who get vaccination of the first or second dose of the AS04 adjuvanted HPV 16/18 vaccine during the recruitment period will be included in the exposed group, and those who are not inoculated with any HPV vaccines before the recruitment will be included in the non-exposed group. All the participants will be visited twice during the study period, one at baseline and the other after a three-year follow-up. A standard questionnaire and cervical cancer screening will be given at each of the two visits to collect information. This whole study process was designed and will be conducted by School of Public Health, Peking University and the CDC of Yinzhou District.

### Study sample and enrollment

This study will enroll the permanent female residents between 9 to 45 years old in the Yinzhou District, with *Cervarix* vaccination history or without any HPV vaccination history.

Subjects who meet the enrollment criteria will be recruited by site investigators at eligible vaccination sites and hospital outpatient clinics for the study. Based on feasibility assessments and historical vaccination data on the YRHIP, baseline recruitment of subjects is expected to continue for 24 months.

### Inclusion criteria

All subjects must satisfy the following criteria at study entry:Permanent female resident in the Yinzhou District (i.e., at least residing in the Yinzhou District for a 3-year period and at least 6 months in every 12-month period).Between 9 and 45 years old at time of the enrollment.Receiving 1 or 2 doses of *Cervarix* (exposed group); or without any HPV vaccination history (non-exposed group).Subjects for whom the investigator believes that they or their parent(s)/ Legally Acceptable Representative(s) (LAR(s)) can and will comply with the requirements mentioned in the protocol (e.g., physically and mentally healthy, be able to complete the baseline and follow-up survey and would comply with the visits, etc.).Written informed consent will be obtained from the subject. For subjects who are below the legal age of consent, written informed consent must be obtained from the parent(s)/LAR(s) of the subject and informed assent must be obtained from the subject according to EC requirement as well as local law. Subjects must understand the protocol and be voluntarily willing to join this study with written informed consent form.

### Exclusion criteria

The following criteria should be checked at the time of study entry. If any apply, the subjects must not be included in the study:Pregnancy at the enrollment.Females with historical cervical diseases (i.e., cervical intraepithelial neoplasia (CIN)1, CIN2, CIN3, and cervical cancer) before the recruitment.After hysterectomy.Females with malignant tumor history or other severe diseases (e.g., liver failure, heart failure, etc.), whose life expectancy is less than 12 months.Females who (1) have historical HPV vaccination, or (2) are in non-exposed groups but have clear intention for HPV vaccination in next 3 years (confirmed by field investigators before enrollment).Any high-risk HPV (hr-HPV) DNA (i.e., HPV 16/18/*31/33/35/39/45/51/52/56/58/59/66/68*) positive result at baseline.Having abnormal colposcope diagnosis or cervical diseases at the baseline screening (women tested HPV positive or having abnormal colposcope diagnosis or cervical disease will be followed up and managed through the local referral system).

### Drop-out criteria

The following criteria should be checked at or right before the follow-up visit. If any become applicable during the study, the subject will withdraw from the study.Pregnancy within the pre-scheduled visiting phase and not eligible for cervical cancer screening.Subjects in the non-exposure group who received any HPV vaccine during the study period.Death due to causes other than cervical cancer.Lost to follow-up (i.e., migrated out the Ningbo city, refusing to respond).

### Sample size

Per the previous research, the effectiveness assumptions for *Cervarix* will be 83%, 66%, and 50% for the cohorts of 9–20, 21–30 and 31–45 years of age respectively [23, 24]. The frequency of exposed group vs. non-exposed group will equal to 1: 1 with the level of significance α = 0.05 and statistic power 1-β = 0.8. The statistical analysis was performed on PASS15.0 (Tests for Two Proportions). Considering the loss to follow-up (5% estimated) and subtraction due to the baseline HPV infection and the contamination during follow-up (25% estimated), there will be 30% loss at the end of study. To mitigate this, the targeting recruitment number will be 1/(1–0.3)*100% of the sample size of effectiveness calculation. The detailed variables and calculation of the sample size is demonstrated in the table below (Table 1).

**Table 1 Tab1:** Sample size calculation

Age group(y/o)	Incidence of HPV 16/18 infection	Vaccine effectiveness	Frequency ratio	Exposure group	Non-exposure group	Sample size for effectiveness calculation	Targeting recruitment number
9–20	0.02	0.83	1:1	661	661	1322	1890
21–30	0.02	0.66	1:1	1208	1208	2416	3452
31–45	0.02	0.50	1:1	2371	2371	4742	6776
Total	-	-	-	4240	4240	8480	12,118

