### Statistical analysis

We will describe the distribution and group differences of the subjects’ general characteristics and the incidence of HPV infection and relevant disease in each age cohort by the exposure status. The categorical data will be described by frequency (proportion) and the Chi-squared test will be performed to show the group difference. The continuous data will be described by mean (standard deviation), and non-normal distribution continuous data will be described by median (quantiles), and then the ANOVA or Wilcoxon rank-sum test will be performed to compare the difference across age groups. Also, the Kaplan–Meier method will be used to draw the survival graph, based on the actual number of cases of each endpoint.

The Logistic Regression will be performed to analyze the impact on HPV 16/18 infection, and HPV 31/33/45 infection in each birth cohort 3 years after vaccination, after adjusting the confounders such as the demographic characteristics, history of sexual behavior, personal behavior history, etc. The vaccine impact will be calculated by using (1-Relative Risk) and its 95% CI.

Stratification analysis will be conducted by frequency of sexual activity, numbers of sexual partners, extramarital sexual activity, family annual income, education level, and cervical cancer screen history. The interaction term between the above factors and HPV vaccination will be introduced into the Logistic regression model, and the differences between the model with interaction term and the model without interaction term will be compared, so as to evaluate the interaction between different factors and HPV vaccination.

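### The crude comparisons of incidence by exposure within wide age bands may be confounded by age; age adjustment is stated only for the regression on HPV 16/18 and 31/33/45

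*Protocol article*

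**What the plan says.** - **Cohorts.** Study design and setting says of the participants: "they will be divided into three age groups (9–20 years, 21–30 years,31–45 years) at baseline". These bands cover 12, 10 and 15 years of age. No finer age balance between exposed and non-exposed women is described.
- **Group sizes.** The Sample size section plans equal groups: "The frequency of exposed group vs. non-exposed group will equal to 1: 1".
- **Descriptive comparison.** The Statistical analysis section describes "the incidence of HPV infection and relevant disease in each age cohort by the exposure status". It gives the chi-squared test for categorical data and Kaplan–Meier curves for each endpoint. No standardisation for age is mentioned.
- **Adjusted model.** The same section plans logistic regression in each cohort, adjusted for demographic and behavioural confounders, and names it for HPV 16/18 and HPV 31/33/45. Strengths of the study adds that age is adjusted in the multi-factor analysis.
- **Objectives.** The Aims section asks for incidence by exposure status for HPV 16/18 (with effectiveness), and, as a second objective, for cervical lesions and the 12 other high-risk types.
- **Age and infection.** The Background reports that "the age distribution of HPV-infected population in China is bimodal (< 25 years and 41–45 years").
- **Age and vaccine access.** The Background says HPV vaccines lie outside the programmed schedule and are paid for by the recipient. Gardasil 9 is for ages 16–26 and Gardasil 4 for 20–45. Some cities offer Cecolin free to girls under 14.

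**The concern.** Women choose whether to be vaccinated, and with which product. Those who took another HPV vaccine belong to neither group. If access to other products changes with age inside a band, the women left as Cervarix recipients and those left unvaccinated may differ in age. If infection also varies with age inside the band, part of the crude difference in incidence is an age difference. It could look like a vaccine effect or hide one.

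The regression can deal with this for the endpoints it names. For cervical lesions and the 12 other high-risk types as a set, the article states only a description by exposure status with crude tests. The crude figures may also carry more weight than their descriptive label suggests, because Study procedure makes the effectiveness assessment exploratory and conditional on sufficient sample size.

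**Working it through.** **1. The plan's own figures.** Inputs from the Sample size section: incidence 0.02 in the non-exposed, effectiveness 83%, 66% and 50%, α = 0.05, power 0.8, ratio 1:1. Two-sided testing is assumed. With p₁ = 0.02, p₂ = 0.02 × (1 − VE) and p̄ their mean,

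n per group = [1.96 √(2p̄(1 − p̄)) + 0.842 √(p₁(1 − p₁) + p₂(1 − p₂))]² / (p₁ − p₂)²

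This gives 658, 1190 and 2319, against 661, 1208 and 2371 in Table 1, all within 3%. Dividing the stated n by 0.7, rounding up and doubling gives 1890, 3452 and 6776, total 12,118, exactly as stated. The size and the ratio are not in dispute.

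**2. Which age limits fall inside which band.**

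| Band | Vaccine access (Background) | Ages of infected women (Background) | Other age-linked features |
|---|---|---|---|
| 9–20 | Limits at 14, 16 and 20 | None inside the band | Baseline HPV test requires sexual debut |
| 21–30 | Gardasil 9 ends at 26 | Below 25 against the rest | – |
| 31–45 | None inside the band | 41–45 against 31–40 | Free screening from 35; additional screenings count for the primary endpoint |

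Each band has at least one reason for concern, but not the same one. The access argument applies to the first two bands only. Both arguments meet only in 21–30.

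**3. How large it could be.** The article gives no age distribution by exposure and no incidence by age within a band, so everything here is assumed. Let the higher-risk ages carry k times the risk of the rest. Let hE and hN be the shares of exposed and non-exposed women at those ages, and let the vaccine effect be the same ratio at all ages.

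Factor on the crude risk ratio = (1 + (k − 1)hE) / (1 + (k − 1)hN)

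Crude effectiveness = 1 − (1 − VE) × factor

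| k | hE / hN | Factor | True 0% | True 50% | True 66% | True 83% |
|---|---|---|---|---|---|---|
| any | equal | 1.000 | 0% | 50% | 66% | 83% |
| 1.5 | 40% / 60% | 1.2/1.3 = 0.923 | 8% | 54% | 69% | 84% |
| 1.5 | 60% / 40% | 1.3/1.2 = 1.083 | −8% | 46% | 63% | 82% |
| 2 | 40% / 60% | 1.4/1.6 = 0.875 | 12.5% | 56% | 70% | 85% |
| 2 | 60% / 40% | 1.6/1.4 = 1.143 | −14% | 43% | 61% | 81% |
| 3 | 40% / 60% | 1.8/2.2 = 0.818 | 18% | 59% | 72% | 86% |
| 3 | 60% / 40% | 2.2/1.8 = 1.222 | −22% | 39% | 58% | 79% |
| 2 | 30% / 70% | 1.3/1.7 = 0.765 | 24% | 62% | 74% | 87% |
| 2 | 70% / 30% | 1.7/1.3 = 1.308 | −31% | 35% | 56% | 78% |

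**4. What age control costs in precision.** An approximate variance inflation is 1/(1 − ρ²), where ρ is the correlation of age part with exposure. A 40/60 split gives ρ = 0.2 and 1/0.96 = 1.04, so intervals are about 2% wider (√1.04). A 30/70 split gives ρ = 0.4 and 1/0.84 = 1.19, about 9% wider (√1.19).

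**The case against.** The strongest reply is that age is already handled where it matters. The effectiveness estimate comes from a model within each cohort, adjusted for demographic characteristics, and the article says that age is adjusted. The plan does not say that it will report the crude effectiveness tabulated above. Banding plus model adjustment is a standard way to control age, and standardised tables may be left to a full protocol or SAP not shown here. This stands for HPV 16/18 and HPV 31/33/45. It does not reach the crude group tests that the article does specify, or the endpoints for which it names no adjusted model.

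Four stronger readings are tempting, and the documents do not support them:

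- **That the incidences are confounded.** This needs a different age mix between the groups within a band. None is reported, and with equal mixes the bias is zero. Licence ages make a difference plausible but do not show one.
- **That the Background shows incident risk varying within bands.** It gives the ages of infected women and names no HPV types. The cohort concerns new infection after women positive for high-risk HPV at baseline are excluded. The only incidence figure in the plan is 0.02 in every band.
- **That the 1:1 ratio or the sample size is at fault.** Both are sound, and an equal ratio creates no confounding.
- **That the study must match on age.** Matching is a design preference that could slow recruitment, and the article already lists long recruitment as a risk. Under the Drop-out criteria, non-exposed women who are later vaccinated are withdrawn. That can shift the age mix again in one group only, so adjustment would still be needed.

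**Conclusion.** The point holds in a limited form. The crude chi-squared and Kaplan–Meier comparisons by exposure, within bands of 10 to 15 years, may be confounded by age. They are least protected for cervical lesions and the full set of 12 other high-risk types, the second objective. The sample size, the ratio and the age-adjusted estimate for HPV 16/18 are not at fault.

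Size and direction cannot be determined from the article. With an assumed 40/60 imbalance and risk ratios of 1.5 to 3, the effectiveness implied by crude incidences moves by about 1 to 4 points at a true 83%, 3 to 8 points at 66% and 4 to 11 points at 50%, in either direction. This rests on two age parts per band and a constant relative vaccine effect. It is an illustration, not an estimate for this study.

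**What to change.** - For every endpoint in each cohort, report incidence by exposure status standardised to the exposed group's age distribution, with a 95% CI, beside the crude figure. Use single years of age or 2–3-year bands. The wider steps suit the youngest cohort: at the planned inputs it expects only about 661 × 0.02 = 13 non-exposed and 661 × 0.02 × 0.17 = 2 exposed events.
- Base between-group statements on the standardised or age-adjusted comparison, not on the crude chi-squared test.
- Extend the age-adjusted regression to cervical lesions and the 12 other high-risk types where event numbers allow.
- Optionally, and only where recruitment is still open, frequency-match non-exposed women to the exposed by birth year. This does not replace the adjustment.

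**Cost.** No extra women, visits or tests; age is already collected. Intervals become slightly wider (about 2% to 9% in the assumed cases above), and there is a little more analysis. The optional matching may slow recruitment at some ages.

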**Fig. 2 Fig2:**
[figure not shown]
Study procedure

Subjects will be stratified into three age groups (9–20 y/o, 21–30 y/o and 31–45 y/o) and divided into exposed and non-exposed groups by vaccination status. The exposed group will include subjects who received 1 or 2 doses of *Cervarix* and the non-exposed group will include subjects who did not receive any doses of HPV vaccine.

During the study period, two visits will be scheduled for all subjects at Month 0 and Month 36, which means the follow-up period will be 3 years. In the first visit, the questionnaire survey will be administrated for all the subjects to obtain the demographic information, sexual history, menstrual and obstetrical histories, etc. For the ones who are eligible for the cervical cancer screening (i, Have sexual debut at the enrollment; ii, no contradiction of screening and iii, are willing to undergo the screening), the type-specific HPV DNA PCR testing will be given within 2 weeks after the enrollment. After 3-years follow-up, the subjects will be called back for the second visit. A questionnaire which measures any changes of behavior during the follow-up period will be performed. Then the second screening with type-specific HPV DNA PCR testing will be given within 2 weeks after the call-back.

At each visit, type-specific HPV DNA PCR testing will be the primary screening approach, and for the ones with unsatisfactory findings (i.e., hr-HPV infection) will be referred to the local abnormal cervical cancer screening results management system for further medical activities (Fig. 1)

By the end of the follow-up period, the prevalence of the HPV infection, cervical disease (e.g., CIN1, CIN2, CIN3, SCC, AIS, etc.) will be described in each birth cohort by their exposure status. If the sample size is sufficient, the effectiveness of *Cervarix* will be assessed as the exploratory objective.

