## Discussion

In order to eliminate cervical cancer during the twenty-first century, WHO recently launched a 90–70-90 target that advocated 90% of girls to be fully vaccinated with HPV vaccines by age 15 years, 70% of women to be screened with a high-performance test, and 90% of women identified with cervical disease received relevant treatment [7]. China is also striving to eliminate cervical cancer through the above methods, of which launching campaigns that promote the vaccination is an important component. Therefore, it is of great value to evaluate the impact of HPV vaccine in China, under the real-world setting. However, in China, only a few women have undergone cervical cancer screening before or just after the vaccination, and it is unclear if they will comply with regular screening later in their life. In this circumstance, it is challenging to acquire sufficient data to evaluate the HPV vaccination impact from a certain baseline and through a certain period of follow-up. Thus, although YRHIP is a high-quality regional database, the existing data are not sufficient to evaluate the impact of HPV vaccination on females aged under 35. This study, therefore, aims to establish prospective birth cohorts to describe the occurrence of HPV infection and related diseases among females in Yinzhou district, and to measure *Cervarix*’s impact in Chinese females.

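### The 80% power for ages 9–20 assumes every remaining participant has an HPV PCR result; the 30% allowance does not cover those never tested

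*Protocol article*

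**What the plan says.** Sample size (Protocol article) sets the test at "with the level of significance α = 0.05 and statistic power 1-β = 0.8", using "The statistical analysis was performed on PASS15.0 (Tests for Two Proportions"). Assumed effectiveness "will be 83%, 66%, and 50% for the cohorts of 9–20, 21–30 and 31–45 years of age respectively". Table 1 enters 0.02 under "Incidence of HPV 16/18 infection" for every cohort. For ages 9–20 it arrives at 661 per group, 1,322 in total, and a recruitment target of 1,890.

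The step from 1,322 to 1,890 is division by 1 − 0.3. The 30% is itemised: "Considering the loss to follow-up (5% estimated) and subtraction due to the baseline HPV infection and the contamination during follow-up (25% estimated").

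Four other places bear on who will have a PCR result:

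- **Inclusion criteria:** entry is from age 9, and sexual debut is not required.
- **Study procedure:** baseline PCR is for those who "Have sexual debut at the enrollment; ii, no contradiction of screening and iii, are willing to undergo the screening".
- **Abstract, Methods:** "If available physically and legally, the cervical cancer screening will be performed".
- **Primary endpoint:** a case is defined by a positive HPV-16 or HPV-18 PCR assay at Month 0, Month 36 or any additional screening. Nothing other than PCR can produce one.

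**The concern.** The allowance is a list, and one item is missing from it. A girl can complete the study, remain unvaccinated if she is in the non-exposed group, and still have no PCR result because she has not had sexual debut or does not want the test. She is neither lost, nor infected at baseline, nor contaminated, so she counts among the 661 while giving no information on the primary endpoint.

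The gap matters most at ages 9–20. This cohort has the smallest sample, the most obvious barrier to testing, and the highest assumed effectiveness (83%). If the power is really well below 80%, a non-significant result there could be misread as absence of effect in the youngest age group.

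The drop-out criteria do treat one kind of untestability as a loss: pregnancy at the scheduled visit that rules out screening. No sexual debut is not on that list. The limitations section names vaccination of controls as the threat to power and does not mention untested participants.

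**Working it through.** **Inputs.** From Sample size and Table 1: α = 0.05, power 0.80, 1:1 allocation, control risk p₁ = 0.02, effectiveness 0.83. Hence p₂ = 0.02 × (1 − 0.83) = 0.0034, the mean risk is 0.0117 and the difference is 0.0166. Sidedness is not stated; two-sided reproduces the plan and one-sided does not (518 per group). The untested share u is not in the documents and is varied as an assumption.

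**1. Reproducing Table 1.** Pooled normal approximation:

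n = [1.960 × √(2 × 0.0117 × 0.9883) + 0.8416 × √(0.02 × 0.98 + 0.0034 × 0.9966)]² / 0.0166²
= [0.2981 + 0.1276]² / 0.00027556 ≈ 657.5, so 658 per group (stated 661).

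Power at 661 is Φ[(0.0166 × √661 − 0.2981) / 0.1516] = Φ(0.849) = 80.2%. Exact enumeration of the uncorrected chi-squared test gives 84%. Recruitment is 661 / 0.7 = 944.3, so 945 per group or 1,890. The other cohorts also reproduce within 3% (1,190 against 1,208; 2,319 against 2,371). The formula and the inflation step are correct.

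**2. Full 30% used, then a further share u never tested.** Tested per group = 661 × (1 − u):

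| u | Tested per group | Expected cases, non-exposed / exposed | Power, approximate | Power, exact |
|---|---|---|---|---|
| 0% | 661 | 13.2 / 2.2 | 80% | 84% |
| 10% | 595 | 11.9 / 2.0 | 76% | 80% (79.6%) |
| 25% | 496 | 9.9 / 1.7 | 68% | 71% |
| 50% | 330 | 6.6 / 1.1 | 51% | 53% |

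On the approximation there is almost no slack: 658 / 661 means that an untested share above about 0.5% takes power below 80%. On the exact calculation the crossing is just under 10%.

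**3. Most favourable case: none of the 25% is used at ages 9–20.** 945 × 0.95 ≈ 898 per group remain.

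- Approximate: 658 / 898 = 0.73, so power stays at 80% up to about 27% untested.
- Exact: 80% needs about 601 per group; 601 / 898 = 0.67, so up to about 33% untested.
- At 50% untested: 449 per group, power 64% (exact 66%).

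**The case against.** The defence has real force on several points.

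- **The arithmetic is right.** Table 1 follows from its stated inputs. The problem is an unstated assumption about who is tested.
- **The debut condition is written for Month 0.** The Month 36 test is described without repeating it, and additional screenings count. The relevant share is therefore girls with no PCR result at any time, which is smaller than the share without debut at entry.
- **Part of the 25% may be free.** An untested girl cannot be removed for baseline infection, so this cohort may have slack, as step 3 shows. The plan does not claim this offset, and it does not cover a large untested share.
- **Some refusal may sit in the 5%.** Loss to follow-up includes refusing to respond. That may absorb some unwillingness, but not absence of debut.
- **Effectiveness is called exploratory** in Study procedure, conditional on sufficient sample size. But Aims puts it in the first objective, and Table 1 sizes each cohort for it.

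A reader might also infer stronger things that the documents do not support:

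- *Half the cohort is untestable.* This needs an even age spread and a debut rate, and neither is given.
- *Minors are barred from testing.* The Abstract speaks only of physical and legal availability, and the inclusion criteria provide for parental consent with assent.
- *Untested girls count as non-cases, which halves the 2% risk.* The endpoint defines a case, not the denominator, and nothing says whether 0.02 applies to tested women or to the whole cohort.
- *Participants will decline screening.* The Discussion remark that "it is unclear if they will comply with regular screening later in their life" concerns Chinese women in general and explains why a prospective cohort is wanted; it is background only.

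**Conclusion.** The point stands as a gap in the allowance. The 80% power for ages 9–20 holds only if essentially everyone left after the 30% loss has a PCR result, or if enough of the 25% goes unused to offset those who do not. The protocol states neither, and its own conditions on testing make the first doubtful.

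The size is a range because the untested share is unknown. At 10% to 50% untested, power is about 76% to 51% after the full allowance (exact 80% to 53%). In the most favourable case it stays at 80% or more until about 27% (exact about 33%) are untested. These figures keep the plan's 2% control risk and 83% effectiveness, take the risk to apply to tested participants, and assume equal testing in the two groups.

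It would go too far to say that the cohort is certain to be underpowered or will probably be inconclusive; the documents do not give the figure that would decide it.

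**What to change.** 1. In Table 1, state that 661 / 1,208 / 2,371 per group are participants with an evaluable follow-up PCR result.
2. Add the expected never-tested share for the 9–20 cohort to the allowance as its own item, and say how much of the 25% is expected to be needed at that age.
3. Restate the 9–20 power over a range of untested shares at the current target of 1,890.
4. Base the infection proportion on participants with a PCR result, and do not count never-tested girls as uninfected. Report the tested share by exposure group: this denominator conditions on debut and willingness, which may differ between groups.
5. If the restated power is below 80%, present the 9–20 effectiveness as an estimate with its confidence interval.

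The cost is a less favourable power statement for one cohort and some added wording. No extra enrolment is needed. Nor does the main analysis need to become an estimate pooled over ages, which would displace the birth-cohort objective.
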